### **10.16 Vineland Adaptive Behavior Scales, Third Edition (VABS-III)**

The VABS-III measures adaptive functioning in people from birth to age 90, across the domains of Communication, Daily Living Skills, and Socialization, as well as Motor Skills for the younger age ranges. Each domain is further partitioned into three more specific scales. To illustrate, the Communication domain contains Receptive, Expressive, and Written Communication. Within each scale, items describe a skill or behavior, and the respondent indicates how often the patient exhibits the skill (i.e. not whether the patient can, but whether the patient does). As the VABS-III is a norm-referenced measure based on 3,695 people from birth to 90 years, the respondent's ratings are tallied to yield scale scores, domain scores, and a total score (Adaptive Behavior Composite) that reflect the degree to which the patient is functioning within the age-typical range or has deviated from it. Age equivalent scores can be obtained for each scale; this option is particularly useful for the Motor Skills domain for which norm-based scores can be calculated only up through age 7, thus allowing for quantification of motor impairments in older patients. Test retest reliability ranges between 0.76 and 0.98 across domains. Previous editions of the VABS have been used extensively in MPS research.

### **10.17 Stair Climb**

A 1-flight stair climb will be filmed and evaluated for ease of climb/descent (i.e. amount of assistance, redirection, etc.) and total time required to complete stair climb and descent. Videos will be stored on the secure LI server indefinitely.

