## 4.0 Background

Sanfilippo syndrome, or mucopolysaccharidosis type III (MPS III), is a genetic disorder of metabolism, associated with insufficient production of a lysosomal enzyme crucial for degradation of heparan sulfate. As a consequence, buildup of heparan sulfate causes progressive, irreversible neurodegeneration. There are four variants of MPS III, distinguished by the lysosomal enzyme deficiency: Heparan-N-sulfatase (MPS IIIA),  $\alpha$ -N-Acetylglucosaminidase (MPS IIIB), AcetylCoA:N-acetyltransferase (MPS IIIC) and N-Acetylglucosamine 6-sulfatase (MPS IIID). MPS IIIA and MPS IIIB are the most common subtypes.

Unlike other types of MPS which involve considerable somatic complications, the most significant aspect of MPS III is neurodegeneration which manifests in stages of developmental disruption and decline, defined by Cleary and Wraith. Their 3-stage model involves: 1) developmental delay in cognition and language before age 3-4 years, 2) temper tantrums, hyperactivity, aggression, sleep disorder, and a further loss of cognitive and language function from age 3-4 years to age 8-10 years, and 3) loss of motor function, feeding difficulties, and seizures from age 8-10 years. Recent work has determined that there is a loss of about 15 IQ points per year in children with MPS IIIA who are younger than 6 years and that they do not surpass a mental age equivalent of 30 months. The advancing disease causes the neurobehavioral profile to meet diagnostic criteria for autism^3, and to overlap with Kluver-Bucy syndrome. A study of patients with both MPS IIIA and IIIB in several European countries found comparable patterns of disease progression in the groups, with delayed language development and cognitive decline, as well as disruptive behavior, particularly in children diagnosed before age 5.

The neurobehavioral symptoms associated with MPS III are highly disruptive and distressing to families, have a significant impact on the quality of life for the patient and family, and likely interfere with adjunctive therapeutic attempts at supporting the child. However, despite the universal acknowledgment that these neurobehavioral symptoms are a prominent concern for MPS III, these symptoms have not been the therapeutic target.

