### Secondary Endpoints:

Within individual change over 8-week treatment period (on maximum effective and tolerated dose) compared to change over 8-week observational period, and from Day 0 to Week +36 (i.e. treatment phase) in:

1. Incidence of treatment-emergent adverse events and laboratory values over 36-weeks of treatment to known frequency of anakinra-related AEs in other populations.
2. MDRI comprised of:
  - Sanfilippo Behavior Rating Scale (SBRS): Minimal Clinically Important Difference (MCID) = 0.25 SD for each scale
  - Child Sleep Health Questionnaire (CSHQ): MCID = 1-point change 
  - Autism Parenting Stress Index (APSI): MCID = 0.25 SD for Stress Total 
  - PROMIS Fatigue - Parent Proxy Custom Short Form: MCID = 3-point change
  - Movement disorder (e.g. dystonia, chorea, etc.): Parent reported duration and severity. Change in one of two characteristics for +/-1 score, +/-2 score for change in two of the characteristics.
  - Non-communicating Children's Pain Checklist-Revised (NCCPC-R): MCID = 0.25 SD

The MDRI will be calculated as the sum of scores from the components. Subjects will receive a score for each component of the MDRI listed above. A score of 0 will be given for a change in score less than the MCID. A score of +1 (improvement) or -1 (worsening) will be given for a change in score of  $\geq 1$  MCID and  $< 2$  times MCID. A score of +2 (improvement) or -2 (worsening) will be given for a change in score of  $\geq 2$  and  $< 3$  times MCID. A score of +3 (improvement) or -3 (worsening) will be given for a change in score of  $\geq 3$  times MCID. Seizures and movement disorder outcomes will be scored as described above.

3. Individual Clinical Response (ICR) – 5 most impactful clinical problems reported by the caregiver. Sum using 5-point Likert scale for each ICR element.

4. Gait: Qualitative assessment by physical therapist (i.e. improved, no change, worsened).
5. Stair climb/descent: Time and quality of movement.
6. Sleep Diary (1-week recall): Sum of the number of overnight awakenings, average duration of overnight awakenings, and duration of time for initial sleep onset at bedtime.
7. Stooling Survey.

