### ***10.5 Physical examination and Anthropometrics***

A trained pediatric provider will perform a physical examination at each visit that will include a detailed lymph node assessment. Tanner staging of pubertal development, including breast and pubic hair development in girls, and testicular size and pubic hair development in boys will be performed each study visit.

Standard anthropometric measurements including standing height and weight will be performed. Height or supine length if unable to stand will be measured 3 times standing without shoes. The average of 3 measurements by the same observer using identical technique with a wall-mounted stadiometer will be recorded. Each subject will be repositioned between each measurement. Height standard deviation score (SDS) will be calculated based on the National Center for Health Statistics 2000 data as provided by the Center for Disease Control. Weight to be measured standing, once with subject in light clothing or dressing gown with shoes removed. Height and weight measurements will be used to calculate body mass index (BMI) as weight (kg) divided by height (m^2).

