### **Secondary objective**

Outcome variables include Individual Clinical Response (ICR, 0~25: sum of the top 5 domains on a 5-point Likert scale), Gait analysis results (improved, no change, worsened), Stair climb/descent (time and quality of improvement), Sleep diary (sum of the number of overnight awakenings, average duration of overnight awakenings, and duration of time for initial sleep onset at bedtime), and Stooling survey results. For univariate analyses, similar statistical tests will be used as ones used for the primary objective, depending on the data type of the outcome for comparing two study periods. For multivariate analyses, mixed effect models (linear for continuous outcomes and non-linear such as multinomial logistic regression for categorical outcomes and Poisson (or Negative Binomial regression model, if over-dispersion is apparent) for count outcomes) will be used using 2-4 different time points (pre-observation, 8, 36 week treatment, post-observation periods) as within subject factor. Covariates such as sex and age will be considered in multivariate models if they are found to be statistically significant in changes of outcomes. Sub-scale analyses will be conducted if changes in the composite score are found to be statistically significant or are reached to a clinically meaningful boundary. We expect to have full data without any missing for all outcomes. However, in case of missing data, two imputation methods, i) last observation forward, ii) multiple imputation assuming missing at random, will be considered.

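### The stair-climb time has no value for a child who cannot complete the flight, and the missing-data methods named in Section 12.2 would hide that loss of ability

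*Protocol*

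**What the plan says.** Section 10.17 has two parts. The climb is "evaluated for ease of climb/descent (i.e. amount of assistance, redirection, etc".), and the time is the "total time required to complete stair climb and descent". Section 9.1, item 5 of the secondary endpoints, lists "Stair climb/descent: Time and quality of movement", with change assessed from Day 0 to Week +36. Section 12.2 words the endpoint as "Stair climb/descent (time and quality of improvement").

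The schedule in Section 10.2 places the stair climb at Week -8, Day +1 and Week +36 only. Under the secondary objective, Section 12.2 states "We expect to have full data without any missing for all outcomes" and, if data are missing after all, that "i) last observation forward, ii) multiple imputation assuming missing at random, will be considered". For comparing periods it applies tests similar to those of the primary objective, which include the Wilcoxon signed-rank test.

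On who may be enrolled, Section 5.2 admits patients aged 4 or over with no upper age limit and no ambulation criterion, and Section 5.4 includes adults. Section 5.1 counts difficulty walking among the pre-screening questions. Section 4.0 describes "loss of motor function, feeding difficulties, and seizures from age 8-10 years". Section 10.5 plans for patients who cannot stand: "Height or supine length if unable to stand will be measured 3 times".

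**The concern.** A completion time exists only for a child who completes the task. The protocol foresees patients with poor or declining motor function but gives neither a time nor a grade for being unable. In the data, such a child has a blank time.

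The protocol does state how blanks may be filled, and both named methods suit this case badly. Loss of the ability to climb is the worst result this measure can show, yet both methods replace it with a time from when the child could still climb or a time modelled on children who can. The error is in one direction: it makes the Day 0 to Week +36 change look better than it was. There is no concurrent control group to reveal it.

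**Working it through.** **Step 1. What LOCF does here.** With measurements only at Week -8, Day +1 and Week +36, the last time available to a child who is unable at Week +36 is the Day +1 time. The change is Day +1 minus Day +1 = 0. The standard signed-rank test discards zero differences, so it gives the same result under LOCF as when the child is left out.

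**Step 2. What imputation under missing at random does.** It predicts a time from children with observed times, who by definition completed the flight. The child receives a plausible climbing time.

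**Step 3. The plan's own precision figure.** Section 12.3 gives a margin of error of half an SD for a paired difference with n = 20. The check is t(0.975, 19)/√20 = 2.093/4.472 = 0.47 SD, so the figure reproduces. With 16 scorable children it is 2.131/4 = 0.53 SD.

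**Step 4. Upper bound on the bias.** The protocol gives neither the share who become unable nor the SD of the times, so both are assumptions. Let the change be normal with SD 1 and mean μ (positive = slower), and let the worst share p become unable, with p = 10%, 15% or 20%. Write z for the (1−p) normal quantile and φ for the normal density.
- Mean change among completers = μ − φ(z)/(1−p).
- Mean change under LOCF = (1−p) × the completers' mean.

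| p | φ(z) | Completers, μ = 0 | LOCF, μ = 0 | Completers, μ = 0.5 |
|---|---|---|---|---|
| 10% | 0.1755 | −0.20 | −0.18 | +0.30 |
| 15% | 0.2332 | −0.27 | −0.23 | +0.23 |
| 20% | 0.2800 | −0.35 | −0.28 | +0.15 |

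**Step 5. Effect on the test.** Simulation with n = 20, the two-sided 5% signed-rank test and 6,000 trials per scenario. By Step 1 the completer results also hold for LOCF.
- μ = 0: improvement is falsely declared in about 10%, 19% and 30% of trials for p = 10%, 15% and 20%, against a nominal 2.5%. With inability ranked worst it is about 2%.
- μ = 0.5 SD worsening: power to detect it is about 31%, 22% and 14%, against 54–57% with inability ranked worst. False improvement is at most 0.2%.

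**Step 6. Relaxing the assumption.** Steps 4 and 5 place inability exactly on the children with the largest worsening. If inability instead follows a latent variable correlated with the change, then at μ = 0 false improvement is about 5%, 8% and 9% at correlation 0.5, and about 4%, 5% and 6% at correlation 0.3.

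**The case against.** Two stronger readings are tempting, and the protocol does not support either.
- A reader might infer that children who decline drop out of the endpoint. Under the named methods a child who loses the ability stays in the data set, with a zero change or an imputed time. Only a child unable at every visit leaves the time analysis, and that reduces n and generalisability without biasing within-child change. Nor is the whole endpoint unscorable. The ease and assistance part can record that a child needs more help, an assisted climb can still be timed, and gait is rated separately with a category for worsening.
- A reader might infer that the remaining children will look improved. That needs a true mean change near zero. In a progressive disease the likelier effect is understated decline, and if the remaining children are unchanged they show no change.

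The upper-bound figures also rest on perfect correlation between inability and worsening. Inability may depend on the level of function at entry, and a failed attempt may reflect behaviour.

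A rule for a failed timed task is often left to the SAP, which is not at hand, and Section 12.2 says only that the two methods will be considered. The endpoint is one part of one of seven secondary endpoints in a feasibility-sized, open-label pilot. It does not enter the MDRI or the dose-escalation decision.

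Most of this stands and limits the size of the point, but the core remains. The protocol itself states the expectation of full data and names the two methods, and both hide the event. The ease part has no scale and no grade for being unable, and Sections 9.1 and 12.2 name it differently, so it is not a defined safeguard. The caution in Section 12.2 about secondary results concerns multiplicity and does not address this bias.

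**Conclusion.** The point holds for the time component. No value is defined for a child who cannot complete the flight, such children are foreseeable from the protocol, and the handling named in Section 12.2 would conceal loss of ability. The bias favours treatment, mainly by understating decline. It creates apparent improvement only if the true mean change is close to zero.

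The upper bound is a shift of about 0.20–0.35 SD among completers (0.18–0.28 SD under LOCF) and a false-improvement rate of about 10–30% against 2.5%. It assumes that 10–20% become unable and that they are exactly the children who worsened most. At correlations of 0.3–0.5 the rate is about 4–9%. None of these shares or correlations comes from the protocol. Severity is minor to moderate.

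**What to change.** In Section 9.1, secondary endpoint item 5, and in Section 12.2:
- Score a child assessed as physically unable to complete the climb at the worst rank for that visit. A child unable at both visits counts as no change.
- Analyse the change with the signed-rank test already named.
- Apply neither LOCF nor imputation under missing at random to these children. Keep ordinary missing-data handling for refusal, non-cooperation and missed visits, and record which of these applied.
- Report the numbers able and unable at each visit.

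The cost is a few sentences and one field for the reason a climb was not completed. The climb is already filmed and the assistance already evaluated, so no procedure is added. The downside is that the mean change in seconds becomes a secondary summary among children able at both visits.

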### **10.18 Stool Microbiome**

Ongoing work in the fields of Autism and Alzheimer's Disease have investigated associations between gut dysbiosis, inflammation and neurologic/neurobehavioral changes. We will request a stool sample at Week

-8, Day 1, Week +8, Week+16, Week +36, and Week +44 to assess for any changes in microbiota. If patients are on a probiotic supplement prior to the study, they should remain on a stable dose. Those not on probiotics will be encouraged not to begin supplementation during this trial.

### ***10.19 Lumbar puncture and CSF collection***

**CSF collection will be limited to participants for whom the procedure can be conducted using only mild sedation (one agent, responds to voice; e.g. oral midazolam or lorazepam only) and without use of ultrasound or fluoroscopy.**

In addition, **parents/guardians may opt out of CSF collection** even if their child meets the above criteria due to parental concerns, e.g. potential amplified negative impact of repeated sedation on the brain of their children specific to having a neurometabolic disease.

For those meeting the criteria above and whose parents/guardians consent to CSF collection, CSF will be collected at Day 1, Week 36, and Week 44 for inflammatory (IL-1 $\beta$ , TNF- $\alpha$ ) and GAG (heparan sulfate non-reducing ends I0S0 and I0S6) biomarkers.

CSF will be collected using the following procedures:

1. The subject will be taken to a procedure room where equipment and medications necessary for resuscitation will be in the room. A local anesthetic (lidocaine dose as appropriate) will be administered in the skin and underlying tissue above the chosen interspace. A small spinal needle will be inserted under sterile conditions into the lumbar spinal sac. A small amount of CSF (roughly 5-8 mL) will be collected for biomarker evaluations.
2. Family members will be provided clear instructions regarding the post discharge monitoring of the subject for anticipated adverse events (AE).

### ***10.20 Unscheduled Study Visits***

Additional visits will be scheduled with local physicians as needed throughout the study period to address concerning signs or symptoms reported by subjects.

Subjects may withdraw voluntarily from the study at any time. If a subject opts to discontinue, attempts will be made to schedule and conduct an Early Termination visit for medical assessment.

If a subject withdraws after an AE, they will be followed until resolution of the issue or until their condition is stable. In the event that a subject becomes pregnant, then

discontinuation, reporting, and follow-up procedures outlined in Section 13.0 will be followed.

### 10.21 Safety Procedures

#### Contraceptive Requirements

**Female subjects:** Female subjects who have had menarche must agree to refrain from heterosexual intercourse or use two methods of birth control during treatment and for an additional 1 month after the last dose of anakinra. Two of the birth control methods listed below may be chosen:

- Hormonal contraception
- Male or female condoms with or without a spermicidal
- Diaphragm or cervical cap with a spermicidal
- Intrauterine device (IUD)

If a female subject is suspected of being pregnant, anakinra must be stopped immediately and may not be resumed until absence of pregnancy has been medically confirmed.

**Male subjects:** Male subjects are not required to use birth control during the study.

#### Vital signs

All subjects will be monitored after their dose on **day 1** for 6 hours and **day 2** for 4 hours with vital signs as follows:

|                      |                                                                                                                                                                                                                     |                         |                          |
|----------------------|---------------------------------------------------------------------------------------------------------------------------------------------------------------------------------------------------------------------|-------------------------|--------------------------|
| Screening     | After at least 5 min of rest, subject's vital signs are taken, preferably in sitting position. Vital sign measurements should be repeated and documented 3 times with at least 5 min intervals between assessments. |                         |                          |
|                      | Assessment frequency                                                                                                                                                                                         |                         |                          |
| Dosing visits | 0-2 hr post-dose                                                                                                                                                                                                    | 2-4 hr post dose        | 4-6 hr post-dose         |
| Days 1, 2     | q 15 min ( $\pm$ 5 min)                                                                                                                                                                                             | q 30 min ( $\pm$ 5 min) | q 60 min ( $\pm$ 10 min) |

1. Vital sign measurements are taken once per time point, preferably in a sitting position, after at least 5 minutes of rest.
2. Heart rate, blood pressure, and respiratory rate should be taken and recorded at each indicated time point above.
3. Vital signs may be monitored more frequently or for longer duration post-dose as clinically indicated.

Vitals will also be measured at Screening, Week-8, Week +8, and Week +36. They will be repeated and documented 3 times with at least 5 min intervals between assessments.

#### ***10.22 Drugs used in the research and the purpose of their use, and their regulatory approval status.***

The safety and effects of anakinra treatment of patients with MPS III will be tested in this study. This medication is approved by the Food and Drug Administration (FDA) for other indications but not specifically for MPS III.

#### ***10.23 The source records that will be used to collect data about subjects***

Electronic case report forms using REDCap will be used. The study site personnel will be trained on using REDCap for data entry and will enter clinical data from source documentation. Source documents will include laboratory reports, study diaries, subject records, paper surveys, etc. Any data sent electronically by email or text will be recorded on a paper source document in the subject's study chart.

#### ***10.24 What data will be collected including long-term follow-up.***

No long-term follow-up data will be collected after the subject finished this 52-week study.

#### ***10.25 Subject Compensation***

The study will arrange and pay directly for airfare and hotel, and provide vouchers for taxi service for travel in the Los Angeles area related to study visits, for the participant and up to two caregivers. Total travel expenses will be covered up to \$2,000 per visit.

Families will also receive a gift card to compensate them for their time and the inconvenience of taking part in the study. The amount for each visit is as follows: Screening/Baseline (\$320), Day 1 (\$375), Week 8 (\$250), and Week 36 (\$250). They will receive a total of up to \$1,195 if they complete the entire study. If they are unable to complete the study, the study will pay for only the visits that were completed.

